## Program Design

2

COPILOT‐HF is a pragmatic, randomized, open‐label intervention trial to investigate the comparative effectiveness of two remote care strategies on optimizing the prescription of GDMT in patients with HF (Figure 1). The first strategy is an “education‐first” approach in which the intervention is provider and patient education with the intention of improving patients' understanding of their diagnosis and its management to increase acceptance and compliance of medical therapy. At 3 months postrandomization, this is followed by a remote clinic that implements a standardized, stepped‐approach to GDMT optimization. In the second approach, provider and patient education is started simultaneously with remote GDMT management clinic. The trial is registered at: https://clinicaltrials.gov/study/NCT05734690.

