### Randomization

2.2

Once a patient agrees to participate in the program, they are randomized in a 1:1 manner at the patient level into either (1) the “education‐first” arm (3‐month period of patient and provider education, followed by enrollment in a remote HF medication management program for the optimization of GDMT) or (2) the “simultaneous” arm (parallel participation in patient and provider education and enrollment in a remote HF medication management program for the optimization of GDMT). Education consists of curated print and video microlearning content for patients and providers' notification regarding their eligibility for GDMT before active participation in the remote management GDMT clinic. For patients enrolled with LVEF < 50% not on SGLT2i at baseline, we will perform a secondary randomization to test a strategy of medication titration sequencing using SGLT2i first versus traditional titration sequencing. Traditional titration sequencing is based on approval dates of medications and guideline sequencing and follows the order of BB, ARNI/ACEi/ARB, MRA, and SGLT2i. Patients will be stratified by LVEF (≥ 50% and < 50%) and by enrollment category, either outpatient or post‐hospital discharge (defined as within 30 days of discharge) for prespecified secondary analysis. All randomizations will be completed through computer‐generated algorithms using block randomization with block sizes of 30 without stratifying based on LVEF to ensure an equal number of patients in each group. The randomization allocation based on the blocks will be concealed to the study personnel.

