**Other efficacy and safety endpoints**			
Process metrics	Number of new GDMT medication classes added	Absolute count of new classes initiated.	6
	Percent reaching maximum tolerated dose	Proportion of patients at maximum tolerated dose for each GDMT class.	6
	Percent on ≥ 50% recommended dose	Proportion of patients on at least 50% of the recommended target dose for each class.	6
	Prescription for four optimal‐dose classes	Proportion of patients with LVEF < 50% who have a prescription for all four GDMT classes at optimal dose.	6
	Utilization of four optimal‐dose classes	Proportion of patients with LVEF < 50% with self‐reported utilization of all four GDMT classes at optimal dose.	6
	Prescription for SGLT2i	Proportion of patients with LVEF ≥ 50% with a prescription for an SGLT2i.	6
	Utilization of SGLT2i	Proportion of patients with LVEF ≥ 50% with self‐reported utilization of an SGLT2i.	6
	Prescription for ARNI/MRA/SGLT2i	Proportion of patients with LVEF 50%–59% with a prescription for ARNI, MRA, and SGLT2i.	6
	Utilization of ARNI/MRA/SGLT2i	Proportion of patients with LVEF 50%–59% with self‐reported utilization of ARNI, MRA, and SGLT2i.	6
	Any worsening HF	Composite of worsening NYHA functional class or hospitalization for HF.	6
Surrogate clinical outcomes	Weight change	Change from baseline (kg).	6
	Blood pressure	Change from baseline (mmHg).	6
	NT‐proBNP	Change from baseline (pg/mL).	6
Clinical outcomes (efficacy and safety)	Any worsening HF	Composite of worsening NYHA functional class or hospitalization for HF.	6
	Hypotension	Systolic blood pressure < 90 mmHg with associated symptoms.	6
	Hypo/hyperkalemia	Serum potassium < 3.0 mmol/L or > 6.0 mmol/L.	6
	Acute kidney injury (AKI)	Increase in serum creatinine by ≥ 1.5 times the baseline value.	6
	Any hospitalization	All‐cause hospitalization.	6
	Death	All‐cause mortality.	6
Health utilization outcomes	Emergency department visit	All‐cause and HF‐specific.	6
	Hospital admission	All‐cause and HF‐specific.	6
	*Patient & provider‐reported outcomes*		
	Patient satisfaction	Net promoter score (NPS) survey.	6
	Provider satisfaction	Assessed via survey.	6
Exploratory outcomes	GDMT medication prescriptions	Analysis of prescription patterns at multiple time points.	1, 2, 6, and 12
	Cost‐effectiveness analysis	Economic analysis of the intervention.	12
	Heart failure collaboratory GDMT score	Change from baseline (for patients with LVEF < 50%).	6

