	Optimization potential score	Change from baseline (for patients with LVEF < 50%).	6

Abbreviations: ACEI, angiotensin‐converting enzyme inhibitor; AKI, acute kidney injury; ARB, angiotensin II receptor blocker; ARNI, angiotensin receptor‐neprilysin inhibitor; BB, beta‐blocker; GDMT, guideline‐directed medical therapy; HF, heart failure; LVEF, left ventricular ejection fraction; MRA, mineralocorticoid receptor antagonist; NPS, Net Promoter Score; NT‐proBNP, N‐terminal pro‐B‐type natriuretic peptide; NYHA, New York Heart Association; SGLT2i, sodium‐glucose cotransporter‐2 inhibitor.

The secondary endpoint is any intensification of GDMT at 3 months, which includes any initiation or titration of a GDMT medication. Intensification of GDMT, which includes any initiation or titration of a GDMT medication, will be captured as the number of intensification steps and compared between treatment groups. For example, the initiation of any dose of an ACEi, followed by two titrations and the initiation of SGLT2i, would count as four intensification steps. We will then compare the primary and secondary outcomes between groups at 6 months postenrollment after all patients receive the remote HF clinic intervention. Patients will be followed actively for 6 months or to the end of active medication management; however, we will continue to obtain data from EHR for another 6 months and compare outcomes at 12 months postenrollment to assess the durability of the results. An interim analysis will be performed after 100 participants have completed 4 months of the program to assess if any changes to the study design are needed based on efficacy, safety, and operational metrics.

The primary analyses will be performed according to the intention‐to‐treat principle, using data for all randomized patients. The “education‐first” group will be compared with the “simultaneous” medication titration and education groups. Sensitivity analyses will be performed in patients engaged in the program for at least 3 months, and in patients who complete the treatment program.

For the second randomization in participants with HFrEF comparing different sequencing of therapies, we will analyze primary and secondary outcomes by comparing patients in the “SGLT2i‐first” and “traditional pathway” GDMT sequencing groups.

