The roll over from education‐first to simultaneous education and medication management at 3 months in a clinical trial of HF is an important aspect of the trial design. The “education‐first” allows for an “enhanced standard of care” with notification of both patients and providers of their eligibility for these medication classes—and education to both patient and provider of the rationale for these recommendations. By allowing patients to roll over to the medication management arm, both providers and patients will not be left without appropriate prescriptions for guideline‐directed medical therapy even if these are not prescribed by their regular care team. It will allow for a period of randomized comparison between groups. HF patients may benefit from an incremental approach to treatment, especially if they are not acutely ill. Starting with education allows patients to gain knowledge about their condition and the importance of adherence to treatment regimens. After this initial period, introducing medication management gradually may help patients better understand and accept the necessity of their medications. This phased approach might enhance patient engagement and long‐term adherence. The roll over at 3 months allows for an assessment of the safety and tolerability of medications, particularly if patients in the education‐first arm are not already on these medications. This analysis can inform decisions about the most effective treatment approach. The analysis at 6 months will assess for the ability of the education‐first group to demonstrate any effects of education pre‐treatment on treatment uptake or adherence to therapy. This period, with enough time to complete full titration with multiple months of buffer, will assess for any differences in uptake or adherence to therapy at what would be a steady state after the initiation and titration period for both groups. Many of the traditional medications used for the treatment of HFrEF can cause hypotension—often limiting further initial titration of GDMT—or hyperkalemia, which also often causes a slowdown or cessation of attempts by providers to continue with GDMT initiation and titrations. By starting therapy with an SGLT2i—a class of medications known to have little effect on blood pressure, as well as a mild reduction in serum potassium, we believe that starting with SGLT2i may mitigate both hyperkalemia and hypotension‐related treatment gaps.

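### Safety, clinical, surrogate, utilization and cost outcomes are read only after the control arm has entered the clinic, and the month-6 contrast is read as an education effect although titration time differs by arm

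*Protocol article*

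**What the plan says.** **Roll-over.** Program Design says of the education-first arm: "At 3 months postrandomization, this is followed by a remote clinic that implements a standardized, stepped‐approach to GDMT optimization". For the other arm: "In the second approach, provider and patient education is started simultaneously with remote GDMT management clinic". Section 2.2 (Randomization) repeats this, giving the education-first arm a "3‐month period of patient and provider education, followed by enrollment in a remote HF medication management program for the optimization of GDMT".

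**Time points.** Table 2 assigns month 3 to the primary endpoint alone. Month 6 is the only entry for:
- hypotension ("Systolic blood pressure < 90 mmHg with associated symptoms"), potassium, and acute kidney injury ("Increase in serum creatinine by ≥ 1.5 times the baseline value");
- worsening HF, hospitalization and death;
- weight, blood pressure and NT-proBNP;
- emergency visits, admissions and satisfaction;
- both GDMT scores.

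Cost-effectiveness ("Economic analysis of the intervention") is at month 12. Prescription patterns are at 1, 2, 6 and 12 months. The text of section 2.4 adds the month-6 re-reading, "We will then compare the primary and secondary outcomes between groups at 6 months postenrollment after all patients receive the remote HF clinic intervention", and a 12-month comparison from EHR data. It counts emergency visits, hospitalizations and deaths attributed to adverse drug reactions over the whole follow-up, with no month-3 cut.

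**Interpretation.** The Discussion says the month-3 roll-over permits an assessment of safety and tolerability. It says the month-6 analysis will show effects of education before treatment, at what would be a steady state for both groups: "This period, with enough time to complete full titration with multiple months of buffer, will assess for any differences in uptake or adherence".

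**The concern.** Clinic and education alone are compared without overlap only up to month 3. Every between-arm safety, clinical and utilization reading in Table 2 falls after that, when both arms have been offered titration. The Discussion gives the roll-over a safety purpose, but no safety outcome is read at month 3.

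Two conclusions are exposed. First, a difference in harm or benefit between clinic and education alone may look smaller at month 6 than it is. Second, a month-6 difference in therapy could be credited to, or blamed on, the education lead-in when it reflects 3 months' less titration. The 12-month economic result has the same limit: both arms incur the clinic, so the increment it measures is that of starting it earlier.

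**Working it through.** **The plan's own figure.** The stated power belongs to the month-3 primary comparison: 14% versus 25%, 250 per arm, two-sided 0.05 (Statistical Plan). With the pooled-variance normal approximation, p̄ = 0.195, and

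z = [0.11 × √250 − 1.96 × √(2 × 0.195 × 0.805)] / √(0.14 × 0.86 + 0.25 × 0.75) = (1.739 − 1.098) / 0.555 = 1.155,

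which gives 87.6% power. This agrees with the stated figure of more than 85%. The point below does not depend on it.

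**Titration time.** From Program Design and section 2.2, the clinic opens at month 0 (simultaneous) or month 3 (education-first).
- Month 6: 6 − 0 = up to 6 months, against 6 − 3 = at most 3 months.
- Month 12: 12 months since the clinic opened, against 12 − 3 = 9.

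**The buffer claim.** If multiple months means at least 2, education-first patients must finish full titration in at most 3 − 2 = 1 month. The readable text gives no titration duration. Whatever the duration T, time left after titration is 6 − T in one arm and 3 − T in the other, a gap of 3 months. That gap is harmless only if T is at most 3 and the outcome is flat from then on. Both arms also receive education, so month 6 could at most isolate education before titration from education alongside it.

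**Effect on event outcomes.** The documents give no event rates, so these are assumptions shown as a range.

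*Sustained excess on titration*, with monthly rates a (off) and b (on):
- Month 3: 1 − exp(−3b) versus 1 − exp(−3a).
- Month 6: 1 − exp(−6b) versus 1 − exp(−3a − 3b).

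*Excess only in the first 3 months of titration*, with 6% risk in that period and 2% in any other 3 months:
- Month 3: 6% versus 2%.
- Month 6: 1 − 0.94 × 0.98 = 7.9% in both arms.

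| Assumption | Month 3 (simultaneous vs education-first) | RR | Month 6 | RR |
|---|---|---|---|---|
| 0.5% off, 1% on per month | 2.96% vs 1.49% | 1.99 | 5.82% vs 4.40% | 1.32 |
| 1% off, 2% on | 5.82% vs 2.96% | 1.97 | 11.31% vs 8.61% | 1.31 |
| 2% off, 3% on | 8.61% vs 5.82% | 1.48 | 16.47% vs 13.93% | 1.18 |
| Early excess only, 6% vs 2% | 6.0% vs 2.0% | 3.0 | 7.9% vs 7.9% | 1.0 |

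In the sustained-excess rows the risk ratio, which is the plan's chosen measure, is diluted while the absolute difference barely moves (second row: 2.86 to 2.70 points). The signal is still weaker. With 250 per arm, difference over standard error in the second row is 0.0286 / √[(0.0582 × 0.9418 + 0.0296 × 0.9704) / 250] = about 1.6 at month 3. At month 6 it is 0.0270 / √[(0.1131 × 0.8869 + 0.0861 × 0.9139) / 250] = about 1.0.

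**The case against.** The strongest reply is that the trial randomizes two strategies, education then clinic versus both at once. That contrast stays randomized and by intention to treat at 6 and 12 months. Section 2.4 says openly that both arms will have had the clinic by month 6. This stands: a reader might infer that the later comparisons are invalid, and the documents do not support that. They answer a different question.

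A reader might also infer that a real harm would cancel exactly at month 6. That needs all the excess to fall in the first 3 months of titration and then stop. Cumulative events include months 0 to 3, so a lasting excess is diluted, not erased. Nor does any passage plan to declare that safety does not differ; the plan treats its secondary outcome analyses as exploratory.

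The primary endpoint is protected at month 3. Prescription readings at months 1 and 2 lie inside the education-only window. The interim look after 100 participants complete 4 months mentions safety, but it serves design changes and is not a month-3 between-arm outcome.

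The steady-state premise cannot be fully tested, because the titration rules are in a figure that is not shown. For the primary endpoint, which accepts any dose, and with 60% of patients (100% − the assumed 40% HFrEF) needing only an SGLT2i, 3 months may be enough. That softens the criticism for that endpoint. It does not supply several months of buffer after full titration.

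It may be said that extra cut-offs belong in a fuller document. But Table 2 states time points, and the Discussion states an interpretation. Both are on the page.

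**Conclusion.** The point holds as one of time points and interpretation, and should be corrected before analysis. Table 2 fixes readings that compare immediate with 3-month-deferred clinic. None of its safety, clinical, surrogate, utilization or cost rows compares clinic with education alone before the roll-over. Under assumed sustained excess, risk ratios of 1.48 to 1.99 at month 3 shrink to 1.18 to 1.32 at month 6; full masking is the extreme case. These sizes rest on illustrative rates, not trial data. For point measures such as blood pressure, NT-proBNP and the GDMT scores, the month-6 value is taken after both arms have been offered titration.

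The education-effect reading of month 6 is confounded with titration time (at most 3 months against up to 6), unless outcomes are shown to have levelled off in both arms. The primary month-3 analysis and its power are not affected.

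**What to change.** 1. **Add a month-3 between-arm cut** for outcomes with dated EHR records: death, all-cause and HF hospitalization, emergency visits, prescriptions and GDMT scores. Do the same for hypotension, potassium and acute kidney injury where values exist. Add a caveat that blood pressure and laboratory values may be checked more often in the clinic arm, so these harms may be found more often there. For that reason month 3 should not become the sole comparison for them.
2. **Keep months 6 and 12**, but label them, including cost-effectiveness, as immediate versus 3-month-deferred clinic.
3. **Remove or qualify** the Discussion's steady-state and education-effect wording. Any comparison at equal time since clinic start should be supportive only: the arms then differ in time since randomization, and losses before clinic start affect one arm only.
4. While the time-point column is open, **reconcile the secondary endpoint**, which the text of section 2.4 reads at month 3 and Table 2 at month 6.

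The cost is wording and one added cut-off, largely on dated records. Enrollment is complete, and no design change is needed. Month 3 will have fewer events, and laboratory, NYHA and survey data at that point will be incomplete.

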### Outcomes and Follow‐Up

2.4

The primary endpoint of the study is the percent of eligible enrolled patients who achieve utilization of recommended pharmacotherapy for HF at 3 months after randomization, which includes (1) prescription utilization of all four drug classes (ARNI/ARB/ACEI, SGLT2i, BB, and MRA) at any dose in patients with LVEF < 50% and (2) prescription of SGLT2i in patients with LVEF ≥ 50%. This binary primary endpoint was chosen for its pragmatic simplicity, applicability across both HFrEF and HFpEF populations, and alignment with current guideline‐directed treatment goals. It offers a clear and clinically meaningful measure of successful implementation of foundational therapy that can be consistently interpreted across HF phenotypes. The prespecified primary, secondary, and exploratory outcomes are summarized in Table 2.

**Table 2 clc70222-tbl-0002:** Study endpoints and outcome measures.

Endpoint category	Specific measure	Definition/details	Time point of assessment (months)
Primary endpoint	Utilization of recommended therapy	Percent of eligible patients achieving: LVEF < 50%: Utilization of four GDMT classes (ARNI/ARB/ACEI, SGLT2i, BB, and MRA). LVEF ≥ 50%: Utilization of an SGLT2i.	3
Secondary endpoint	Any intensification of GDMT	Any initiation or dose titration of a GDMT medication.	6

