### Statistical Plan

2.5

We estimate that the baseline percentage of patients with HF who meet the primary endpoint definition will be ~10% [11]. In the education/notification arm, we anticipate a ~4% absolute improvement to ~14% based on other studies with educational interventions that target patients [11]. Based on our previous experience, we hypothesize that a strategy of a remote, navigator‐led, pharmacist‐driven HF program will increase this proportion to 25% at 3 months after randomization. Our prior pilot study of a similar remote, navigator‐led program formed the basis for this estimate [14]. With 250 patients in each strategy group (500 patients in total) there will be > 85% power to detect a significant difference between groups at a two‐sided 0.05 significance level. We estimate a rate of dropout (patients who stop receiving treatment from the program) of 10%. The primary endpoint (as determined by last observed medication use) will be assessed in all patients.

For the second randomization of the sequence of GDMT therapy initiations in patients with LVEF < 50%, we expect that the percentage of patients in the traditional titration sequencing group who meet the primary endpoint will be 15%. Considering an imbalanced enrollment of patients with HFrEF and HFpEF, with 40% of patients with HFrEF, a total of 100 patients in each group will provide 80% power to detect an 18% difference between groups at a two‐sided 0.05 significance level, with an estimated 10% dropout (patients who stop receiving treatment from the program). This assumption is supported by prior real‐world data demonstrating hyperkalemia rates of approximately 28%–38% with traditional GDMT sequencing, as well as clinical trial data showing that SGLT2 inhibitors reduce the incidence of hyperkalemia and hypotension [20, 21, 22] —two common barriers to the initiation and up‐titration of MRAs and ARNIs [23, 24]. Based on these findings, we believe that initiating therapy with an SGLT2i may mitigate these adverse effects and lead to a higher proportion of patients achieving full GDMT in this arm.

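### A 12-month comparison between arms that have both had the remote clinic does not measure whether therapy was kept

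*Protocol article*

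**What the plan says.** The primary endpoint concerns patients "who achieve utilization of recommended pharmacotherapy for HF at 3 months after randomization" (protocol article, Section 2.4). The same section then extends the comparison in two steps:

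- Month 6: "We will then compare the primary and secondary outcomes between groups at 6 months postenrollment after all patients receive the remote HF clinic intervention".
- Month 12: the team will "continue to obtain data from EHR for another 6 months and compare outcomes at 12 months postenrollment to assess the durability" of the results.

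On contact with patients, it says: "Patients will be followed actively for 6 months or to the end of active medication management". After that point the EHR is the only source described.

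Table 2 keeps prescription and use apart. The use measures are self-reported (for example, the proportion "with self‐reported utilization of an SGLT2i") and are listed at month 6 only. The one medication measure that Table 2 lists at month 12 is the exploratory row on GDMT prescriptions, described as "Analysis of prescription patterns at multiple time points" and scheduled at months 1, 2, 6 and 12.

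Section 2.5, in the paragraph on sample size and dropout, adds: "The primary endpoint (as determined by last observed medication use) will be assessed in all patients".

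**The concern.** Durability asks whether patients who reached recommended therapy still have it some months after the program stops managing them. That is a question about the same patients at two times. The article answers it by comparing outcomes at month 12, and the only comparison it describes is between the randomized arms. Because the education-first arm enters the same clinic at month 3, no arm without the clinic remains at month 12.

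The risk is misreading in both directions. Similar arms at month 12 could be reported as a lasting effect, and a smaller difference than at month 3 could be reported as an effect that faded. Neither reading follows. The Discussion says of earlier interventions that it is unclear whether they change prescribing durably, so this trial's own answer should withstand the same question.

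**Working it through.** **1. The plan's own figure.** The article gives no figure for the 12-month comparison. The figure it does give is power above 85% for the 3-month endpoint: 14% v 25%, 250 per arm, two-sided 0.05 (Section 2.5). With pooled variance under the null:

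- mean rate = (0.14 + 0.25)/2 = 0.195
- null SE = √(2 × 0.195 × 0.805/250) = 0.0354
- alternative SE = √((0.14 × 0.86 + 0.25 × 0.75)/250) = 0.0351
- power = Φ((0.11 − 1.96 × 0.0354)/0.0351) = 87.6% (85.1% with continuity correction)

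The stated power reproduces, and nothing below changes it.

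**2. Exposure of each arm** (Sections 2, 2.2 and 2.4; Discussion).

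| Time | Simultaneous | Education-first |
|---|---|---|
| Month 3 | education and clinic | education only |
| Month 6 | clinic received | clinic received, started at month 3 |
| Month 12 | EHR data only | EHR data only |

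Only at month 3 does the contrast separate clinic from no clinic. The Discussion itself treats month 6 as a steady state for both groups.

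**3. What the month-12 arm difference measures.** Let p be the rate on recommended therapy at month 6 and r the share of those patients who still have it at month 12. Leaving out new starts, the month-12 difference is p₁r₁ − p₂r₂. If both arms reach the same p, this equals p(r₁ − r₂). It reflects a difference in retention between arms and not the level of retention. Take p = 25% in both arms (an assumption, borrowed from the plan's 3-month rate for the clinic arm):

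| Retention in both arms | Month-12 rates | Arm difference |
|---|---|---|
| 100% | 25% v 25% | 0 |
| 80% | 20% v 20% | 0 |
| 0% | 0% v 0% | 0 |

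**4. Shrinkage since month 3.** The planned 3-month difference is 25% − 14% = 11 points. If the education-first arm rises to 25% in the clinic and nobody in either arm stops, the difference falls from 11 points to 0. That is crossover with full retention.

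**5. Like-for-like measures.** In Table 2, self-reported use is listed at month 6 and prescription at months 6 and 12. Only prescription can be compared with itself. Setting month-6 self-reported use against month-12 prescriptions would mix a change of measure with a change of therapy.

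**6. If the last-observed rule were used at month 12** (an assumption, not the plan). Let s be true retention and u the share with no informative EHR medication update between months 6 and 12. Carrying the earlier status forward reports u + (1 − u)s, an excess of u(1 − s).

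| True s | u = 10% | u = 20% | u = 30% | u = 50% |
|---|---|---|---|---|
| 90% | 91% | 92% | 93% | 95% |
| 80% | 82% | 84% | 86% | 90% |
| 70% | 73% | 76% | 79% | 85% |

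The excess always runs toward therapy kept, by 1 to 15 points over this grid. The documents give neither s nor u.

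**The case against.** Four points can be made for the plan.

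- **The rates in each arm will be visible.** Section 2.5 compares percentages, so 25% v 25% and 0% v 0% would look quite different beside the month-6 figures. This stands in part. Arm-level rates do reveal a large net loss, but they mix patients who stopped with patients who started. If 80% of a 25% group is retained, the rate falls to 20%. New starts in (0.25 − 0.20)/0.75 = 6.7% of the others would restore it to 25% and hide the loss.
- **A later arm comparison has a purpose of its own.** The Discussion asks whether education before treatment affects uptake or adherence. That stands, and the comparison can be kept for that question.
- **The month-12 sentence does not itself say the comparison is between groups.** True. The reading rests on the sentence before it, which does, and on the following paragraph, which names the two arms as the comparison. No other contrast is described.
- **A journal article leaves detail to the full plan.** That holds for look-back windows and the handling of stale records, whose absence is not criticised here. It does not cover a method and a purpose that the article states together and that do not match.

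Two stronger readings are tempting and are not supported. A reader might infer that the last-observed rule in Section 2.5 governs month 12, so that durability is found by construction. The article ties that rule to the primary endpoint, which is defined at 3 months, and no carry-forward rule accompanies the 12-month sentence. A reader might also infer that EHR data cannot show whether therapy was kept. They can record stops, switches and renewals; they are incomplete, not uninformative.

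**Conclusion.** The point holds as a mismatch between method and purpose. A between-arm comparison at month 12 does not measure persistence of therapy: with equal uptake and equal retention the difference is zero at any retention from 0% to 100%, and the 11-point difference planned for month 3 can vanish through crossover with no loss of therapy. This conclusion needs no assumed stopping rate. It rests on reading the 12-month contrast as between arms and on both arms having received the clinic by then.

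The possible carry-forward bias is conditional. Its direction is known, but its size cannot be fixed from the documents; 1 to 15 points is a range under assumed inputs.

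The importance is moderate. Table 2 classes the month-12 prescription analysis as exploratory, and the 3-month primary test and its power are untouched.

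**What to change.** State durability as a within-arm retention proportion. The denominator is patients on recommended therapy at month 6 (or at the end of active management), and the numerator is those who still have it at month 12. In addition:

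- Use the same EHR prescription measure at both times, and do not carry the earlier status forward.
- Report it descriptively, beside the arm-level rates at months 6 and 12.
- Show a sensitivity range for patients with no recent EHR medication record, from all counted as stopped to all counted as kept. The width of that range is u: for example, with 80% retention among patients with a record and u = 20%, it runs from 0.80 × 0.80 = 64% to 64% + 20% = 84%.
- State that the 12-month between-arm comparison is not read as durability.

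The cost is a change of analysis wording. The EHR data to month 12 are already planned, and no new visits or patients are needed. There are two drawbacks. The denominator is a status reached after randomization, so retention is descriptive within each arm and does not give a randomized contrast. The retention figure may also come out lower than a simpler analysis would show.

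### The sequencing comparison is powered on an endpoint at 3 months after randomisation, when the education-first half has not yet entered the titration clinic; if sequence has no effect there before month 3, power is roughly 34–50%, not 80%

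*Protocol article*

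**What the plan says.** All references are to the protocol article.

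- **Who is randomised to a sequence.** Section 2.2 defines the group as enrolled patients with LVEF below 50% who are "not on SGLT2i at baseline, we will perform a secondary randomization to test a strategy of medication titration sequencing". Nothing limits it to the simultaneous arm.
- **Size and power.** Section 2.5 assumes a trial of 500 "with 40% of patients with HFrEF" and states that "a total of 100 patients in each group will provide 80% power to detect an 18% difference between groups". The assumed rate is given as "the percentage of patients in the traditional titration sequencing group who meet the primary endpoint will be 15"%, so the SGLT2i-first group is taken to reach 33%. The test is two-sided at 0.05, "with an estimated 10% dropout (patients who stop receiving treatment from the program").
- **Endpoint.** Section 2.4 states: "For the second randomization in participants with HFrEF comparing different sequencing of therapies, we will analyze primary and secondary outcomes by comparing patients" in the two sequencing groups. No separate time point is given. Section 2.4 and Table 2 place the primary endpoint at 3 months after randomisation. For LVEF below 50% it requires all four drug classes.
- **When titration starts in the education-first arm.** Section 2 describes the education phase and continues: "At 3 months postrandomization, this is followed by a remote clinic that implements a standardized" programme of GDMT optimisation. Section 2.2 describes the same order.
- **A later comparison.** Section 2.4 also plans to compare the primary and secondary outcomes between groups at 6 months, once everyone has had the remote clinic. That sentence comes before the sequencing paragraph and does not mention sequencing.

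**The concern.** A sequencing strategy can act only on patients who are being titrated under it, and in this trial the pharmacist-led remote clinic does the titrating. Allocation to the strategy arms is 1:1, so about half of each sequencing group is in the education-first arm and is only just reaching the clinic when the primary endpoint is read. Those patients add noise but probably little or no contrast. The power statement makes no allowance for this.

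Sequencing is one of the two aims set out in the Introduction. If the month-3 reading is the main one, a true effect of the planned size would be missed at least half the time. The estimated difference would be about half of what the sequence achieves in treated patients.

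**Working it through.** **1. Are both strategy arms pooled?** 40% of 500 is 200, or 100 per sequencing group. The simultaneous arm has 250 patients, of whom 40% is 100 in total, or 50 per sequencing group. The stated 100 per group therefore needs both arms.

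**2. Formula.** Two-proportion normal approximation with pooled variance under the null, two-sided 0.05:

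power = Φ[(d − 1.96·s0)/s1], with d = p2 − p1, p̄ = (p1 + p2)/2, s0 = √(2p̄(1 − p̄)/n), s1 = √([p1(1 − p1) + p2(1 − p2)]/n).

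**3. The plan's own figure.** p1 = 0.15, p2 = 0.33, n = 100 × 0.9 = 90. Then s0 = 0.0637, s1 = 0.0622, and (0.18 − 0.1248)/0.0622 = 0.887, giving 81.3%. With n = 100 it is 85.2%. The stated 80% is reproduced.

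**4. Dilution.** Let e be the month-3 rate in the education-first half, the same in both sequencing groups. The pooled rates are (e + 0.15)/2 and (e + 0.33)/2. Their difference is 0.18/2 = 0.09 whatever e is.

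**5. Choice of e.** Section 2.5 gives about 14% for the education arm, but that figure covers all LVEF groups and starts from a 10% baseline. Everyone in the second randomisation is off SGLT2i at entry and has LVEF below 50%, so none can meet the four-class endpoint at baseline. Starting from 0% and adding the plan's 4-point education gain gives 4%. The document gives no rate for this population, so I show a range.

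| e | Pooled rates | Power, n = 90 | Power, n = 100 |
|---|---|---|---|
| 14% | 14.5% vs 23.5% | 33.6% | 36.7% |
| 10% | 12.5% vs 21.5% | 36.1% | 39.4% |
| 4% | 9.5% vs 18.5% | 41.2% | 44.9% |
| 0% | 7.5% vs 16.5% | 45.9% | 49.9% |

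Example, first row, n = 90: s0 = 0.0585, s1 = 0.0581, (0.09 − 0.1146)/0.0581 = −0.424, giving 33.6%.

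**6. Simultaneous arm alone at month 3.** With 45–50 per group and 15% vs 33%, power is 52–56%. Dropping the education-first half does not restore 80%.

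**7. If some sequence effect is present early.** Suppose the education-first half shows a fraction f of the 18 points by month 3, with 15% in the traditional group. Power at n = 90 and n = 100 is 46% and 50% for f = 0.25, 59% and 64% for f = 0.5, and 71% and 76% for f = 0.75.

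**The case against.** **The 6-month comparison may be the one intended.** The sequencing paragraph names no time point, and the 6-month sentence uses the same words for the outcomes. Table 2 lists the secondary endpoint at 6 months although the text of section 2.4 says 3, so timing is unsettled for that endpoint too. This is the strongest point, and it shows that a suitable assessment already exists. But the power statement rests on meeting the primary endpoint, which is fixed at 3 months, and the 6-month sentence is not linked to sequencing.

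**The clock might restart at clinic entry.** The article does not say when the second randomisation takes place, and the design figure is not available here. If the 3 months ran from clinic entry, there would be no dilution. The text counts from randomisation, however, so the wording would have to change even then.

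**The 15% and 33% may already be pooled rates.** With 14% in the education-first half, the clinic-managed half would need 2 × 0.15 − 0.14 = 16% and 2 × 0.33 − 0.14 = 52%, averaging 34%. With 0% it would need 30% and 66%. The plan expects 25% in the managed arm (an all-LVEF figure), and nothing in the article supports 52% or more.

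**No effect before month 3 is an assumption.** This stands. Section 2.3 says that providers are sent a medication algorithm, and the article does not say whether it follows the assigned sequence. The 34–50% is conditional on no early effect; step 7 shows how it moves.

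**Readings that go too far.** A reader might take 34% as the power of this comparison. That is the lowest value in the table and depends on a 14% rate that does not fit patients who are all off SGLT2i at entry. A reader might also infer that a null result would say nothing about sequencing. The simultaneous half would still be informative at month 3, and the 6-month data may be informative for everyone.

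**Conclusion.** The concern holds in conditional form. Population, endpoint time and clinic entry, as written, do not fit together with 80% power. If sequence has no effect in the education-first half before month 3, the detectable contrast is halved to 9 points and power is about 34–46% with 90 per group, or 37–50% with 100. The conclusion does not depend on the exact education-first rate: every value from 0 to 14% leaves power at or below 50%. It does depend on reading the endpoint at 3 months after randomisation and on roughly equal numbers from the two strategy arms. The comparison of the two strategy arms, and its power, are not affected.

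**What to change.** Before the comparative analysis:

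1. Set the sequencing endpoint at a time when both arms have had the clinic. One option is 3 months after clinic entry (month 3 for the simultaneous arm, month 6 for education-first). The other is the month-6 assessment already planned for everyone.
2. Stratify the sequencing test by strategy arm.
3. Keep the comparison at 3 months after randomisation as a sensitivity analysis in the simultaneous arm.
4. Restate the power for the chosen time point, giving the rates assumed in each strategy arm for patients off SGLT2i at entry.

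No new data are needed, because outcomes at months 3 and 6 are already planned. The cost is a late change: enrolment is complete, so the change must be justified, dated and disclosed. The first option compares patients at different calendar times. The second leaves unequal time on sequence (6 months against 3). Stratifying by arm deals with either.
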